### PA, expressive activities and burnout/vigor at work

Nordic walking was chosen because while it allows moderate to vigorous energy expenditure [30], it does not require particular physical qualities, or expensive equipment. Moreover, this activity has been identified as efficient in decreasing fatigue states [31] and there are numerous examples of the successful implementation of walking interventions in the work setting (for a review, see [32]). Comparing participants doing Nordic walking with those in the waiting list control condition enables us to test the effect of PA on burnout and vigor compared to the natural development of these affective states during the same period at work. Based on available research, we hypothesize:*Hypothesis 1a:* the PA intervention is effective in reducing burnout and/or improving vigor at work compared to the waiting list control condition.

In addition to the PA condition, we have included an expressive activity condition (Theatre condition) to compare the effects of two leisure activities, with only one requiring high energy expenditure (Nordic walking). Sonnentag and her colleagues recently recommended that future studies should examine whether employees who engage in creative and cultural activities in their free time report a higher level of well-being thereafter, and recover faster and more effectively from work, than other employees [33]. Indeed, some correlational studies [34, 35] showed positive relationships between the frequency of creative and cultural activities during leisure time and recovery experiences and work engagement. As far as we know, no workplace interventions have examined the effectiveness of expressive activities or compared effects of PA and expressive activities on burnout/vigor. While both activities induce psychological mechanisms explaining improvements in work-related well-being (see below), regular PA leads to additional biological adaptations which could contribute to reduced physiological reactions to stressors [36, 37]. The combination of these psychological and physiological benefits in PA could lead to higher effects on burnout/vigor compared to expressive activities. Consequently, we expect that:*Hypothesis 1b:* the Theatre condition intervention is effective in reducing burnout and/or improving vigor at work*Hypothesis 2:* PA is more effective than Theatre condition in reducing burnout and/or improving vigor at work

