
### Physical Activity and Secondary Outcomes

In addition to burnout and vigor, we will assess the consequence of the different conditions on four secondary outcomes, to check whether PA might also have other positive consequences on important job-related variables. First, we will examine the effects of the intervention on *job satisfaction*. This variable refers to a “pleasurable or positive emotional state resulting from the appraisal of one’s job or job experiences” [44]. Thøgersen-Ntoumani et al. [28] showed that participants in a workplace PA program experienced greater levels of enthusiasm and relaxation at work during the afternoon when they carried out PA during lunchtimes compared to the days when they did not. Then, by referring to SDT [45, 46], we will examine the effect of the intervention on the quality of *work motivation*, namely on autonomous (when the professional activities are experienced as emanating from one’s self) or controlled (when they are experienced as emanating from internal or external pressures) motivation. Such motivations are important to study because they are related to a host of cognitive, affective and behavioral consequences such as well-being, job satisfaction, organizational commitment, workaholism, burnout and turnover intentions [47, 48]. We will also investigate the effect of PA intervention on *work ability*. This refers to the “physical, psychological, and social capability of a worker to perform and interact within their work, and the individual’s specific work demands, health conditions, and mental resources” [49]. It has been demonstrated that burned-out people report decreased work ability [50], and an intervention study [37] reported that a six-week physical activity program improved work ability. Finally, we will study the effect of the intervention on the self-reported *work performance*. This variable refers to work-related activities expected of an employee and how well these activities were executed [51]. A few previous studies [52, 53] have reported that more physically active employees reported higher self-rated work productivity, and that a walking program in the workplace over sixteen weeks [54] increased work-performance by the end of the intervention.*Hypothesis 4:* the PA intervention is effective in improving job satisfaction (H4a), autonomous work motivation (H4b), work ability (H4c), and work performance (H4d).

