### Weekly trajectories of employee burnout, vigor, and psychological recovery mechanisms

Following the recommendations by de Vries and colleagues [29, 66], we will examine the employees’ well-being and recovery trajectories during the course of the trial in order to answer two questions: (a) what is the minimum exposure to exercise or Theatre condition required for burnout and vigor to differ between interventions and control conditions? and (b) are the feeling of having recovered and the experiences of recovery among participants in PA and Theatre condition related to differences in their vigor and burnout trajectories? To be able to answer these questions and provide a finer grain of analysis on the development of well-being indicators during the intervention and on the relationships between these indicators and the recovery mechanisms, during each week of the intervention we will assess the primary outcomes (burnout, vigor) and the psychological mechanisms of recovery (detachment, relaxation, mastery, control, relatedness, and positive affects experiences) using single-item scales. While it is difficult to predict precisely when the well-being indicators will change as a function of the intervention, we nevertheless expect that:*Hypothesis 6a:* Participants in the PA and Theatre conditions report a decrease in feelings of burnout and/or an increase in vigor each week over the intervention period compared to participants in the control condition.*Hypothesis 6b:* Participants in the PA-need-supportive style conditions report a decrease in feeling of burnout and/or an increase in vigor each week over the intervention period compared to participants in the PA-traditional style and Theatre conditions.

Regarding the relationships between recovery and burnout/vigor trajectories, we expect that:*Hypothesis 6c:* Participants in intervention groups who experience greater feelings of psychological detachment from work, relaxation, mastery, control, relatedness, or positive affects experiences during the sessions, show a larger improvement in their weekly burnout and/or vigor trajectories compared to participants who experience lower feelings during these sessions.

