### Statistical analysis

#### Analyses of Primary and secondary outcomes

Between-arm differences in changes on the primary and secondary outcomes will be analyzed using generalized linear mixed models (GLMM) according to intention-to-treat and per-protocol principles. Intention-to-treat analyses [91] refer to the effect of treatment “as assigned”, meaning that all participants who are randomized to a condition will be included in the analyses, regardless of dropout or missing values. By contrast, per-protocol analyses refer to the effect of treatment “as received”, excluding only participants who have less than 50% compliance to the 20 sessions in the intervention. GLMM has several advantages over repeated measures ANOVA as it considers the hierarchical nature of the data and can accommodate missing data [92]. To distinguish between short- and long-term intervention effects, two separate series of GLMM analyses were performed for each outcome variable. Two time points (pre and post) were used to determine short-term intervention effects and four time points (pre, post, three- and four-month follow-ups) were used to examine long-term intervention effects. Regarding the short-term intervention effects, differences in changes on the outcome variables as a function of the group allocation will be assessed with models including group, time, and group x time interaction as fixed effects. For the group allocation, contrasts analyses [93] will also be carried out to test our hypotheses (H1 – H4) specifically. For that, three contrasts will be computed. The first one will compare the WLC condition with the Theatre condition, PA-TS and PA-NSS conditions (respectively coded as − 0.75, + 0.25, + 0.25, + 0.25) to test whether doing a leisure activity (PA or Theatre conditions) at the workplace leads to a reduction in burnout and an improvement in vigor (H1a, H1b). The second contrast will compare the Theatre condition with the PA-TS and PA-NSS conditions (respectively coded as − 0.667, + 0.333, + 0.333, while WLC will be coded 0) to test whether PA is more effective than theatre condition (H2) in reducing burnout and improving vigor. Finally, the third contrast will compare the PA-TS condition with the PA-NSS condition (respectively coded as − 0.50, + 0.50, while WLC and Theatre conditions will be coded 0) to test whether the positive effect of PA is more pronounced when the instructor uses a need-supportive style (H3). The same analyses will be performed to examine if the effects of the intervention are still effective three months (T12) and six months (T13) after the end of the intervention period. Since there are more than two-time measurements per participant, we will allow random intercepts for participants and random linear slopes for the repeated measurements at the level of participants. These random effects will allow us to estimate each participant’s outcome variables and the rate of change of these outcomes over time. In all analyses we will control for a number of variables that could influence participants’ outcomes. These include job characteristics, and needs satisfaction-frustration at work. Finally, an estimate of the effect size for each outcome will be reported using the conditional pseudo R^2^, which will be computed using the MuMin package of the R software [94].

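### Contrast 1 pools Theatre with both PA arms, so no planned contrast tests PA alone (H1a, H4) or Theatre alone (H1b) against the waiting list

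*Protocol article*

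**What the plan says.** The background section of the protocol article states two separate hypotheses. H1a is that "the PA intervention is effective in reducing burnout and/or improving vigor at work compared to the waiting list control condition". H1b is that "the Theatre condition intervention is effective in reducing burnout and/or improving vigor at work"; it names no comparator but concerns Theatre alone. H4, on the secondary outcomes, is again about PA only: "the PA intervention is effective in improving job satisfaction (H4a"), and likewise for the other three outcomes.

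The section on analyses of primary and secondary outcomes says that contrasts will test H1 to H4 specifically, and fixes their number: "For that, three contrasts will be computed".

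- Contrast 1: "The first one will compare the WLC condition with the Theatre condition, PA-TS and PA-NSS conditions", coded −0.75 for the waiting list (WLC) and +0.25 for each of the other three arms. Its stated purpose is to see whether a leisure activity "leads to a reduction in burnout and an improvement in vigor (H1a, H1b").
- Contrast 2: Theatre −0.667, PA-TS and PA-NSS +0.333 each, WLC 0, "to test whether PA is more effective than theatre condition (H2").
- Contrast 3: PA-TS −0.50, PA-NSS +0.50, WLC and Theatre 0, for H3.

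No contrast carries an H4 label. The mediation section and the weekly-trajectories section reuse the same three contrasts.

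**The concern.** H1a and H1b are questions about particular arms, and one pooled number cannot answer both. Contrast 1 is the only contrast in which the waiting list has any weight, so everything the trial will formally say about an activity against no activity goes through the average of three arms. An effect confined to PA moves that average and, under the H1b label, would count towards Theatre. An effect confined to Theatre would likewise count towards PA.

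H1a belongs to the trial's first objective, on both primary outcomes, and the article presents the Theatre comparison as new. If the arm-specific comparisons are not planned, they become post hoc once the data are seen.

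**Working it through.** **1. What contrast 1 estimates.** Inverting the coding matrix (intercept plus three contrasts) gives these weights on the arms in the order WLC, Theatre, PA-TS, PA-NSS:

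- C1 = (−1, 1/3, 1/3, 1/3)
- C2 = (0, −1, 1/2, 1/2)
- C3 = (0, 0, −1, 1)

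C1 is therefore (Theatre + PA-TS + PA-NSS)/3 − WLC. The arm-specific comparisons are combinations of contrasts that the plan does not form:

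- PA − WLC = C1 + C2/3
- Theatre − WLC = C1 − (2/3)·C2

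**2. The plan's own sample size.** Inputs from the sample-size section: d = 0.35 (f = d/2 = 0.175), power 80%, alpha 0.025, correlation 0.5, four groups, 25% dropout. For a group × time interaction with two time points, λ = f²·N·2/(1 − 0.5), with 3 and N − 4 degrees of freedom. This needs N = 111, or 112 with equal arms, and 112 × 1.25 = 140. The stated figure is reproduced, and it was sized on the overall interaction, not on any contrast.

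**3. Effect sizes on the change scale.** With correlation 0.5, the SD of the pre-post change is √(2(1 − 0.5)) = 1 outcome SD. Then λ = 0.175² × 4 × N = 0.1225·N, so f on change scores is √0.1225 = 0.35. If Theatre is inert and both PA arms shift by d, the SD of the four arm means is d/2, which gives d = 0.70. If all three activities shift equally, it is 0.433d, which gives d = 0.81. The value that belongs with an inert Theatre arm is 0.70. The value 0.35 is the figure the article prints, here read literally as PA against WLC.

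**4. Rejection probabilities with Theatre inert.** Expectations: C1 = (0 + d + d)/3 = 2d/3; PA − WLC = d; Theatre − WLC = 0. Standard errors with n per arm: C1 √((1 + 3/9)/n); PA − WLC √((1 + 0.5)/n). At n = 26.25 (35 × 0.75) these are 0.225 and 0.239; at n = 35 they are 0.195 and 0.207. Two-sided 0.025, favourable direction, non-central t with 4(n − 1) degrees of freedom:

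| d | n per arm | C1 | PA vs WLC | Theatre vs WLC |
|---|---|---|---|---|
| 0.35 | 26.25 | 11% | 21% | 1.25% |
| 0.35 | 35 | 14.5% | 29% | 1.25% |
| 0.70 | 26.25 | 42% | 74% | 1.25% |
| 0.70 | 35 | 55% | 87% | 1.25% |

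Example for d = 0.70, n = 26.25: C1 has non-centrality 0.467/0.225 = 2.07 against a critical value of 2.28, giving 42%.

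**5. The reverse case.** If only Theatre works, C1 has expectation d/3 and is significant in 4% to 5% of trials at d = 0.35 and in 11% to 14.5% at d = 0.70, with no PA effect.

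**6. If all three activities work equally.** At d = 0.70 and 26.25 per arm, C1 has 80% power against 74% for PA vs WLC. Pooling then helps slightly.

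**The case against.** Four points on the other side deserve weight.

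*The article never says that a significant contrast 1 proves Theatre works.* True. It describes contrast 1 as being about a leisure activity, PA or Theatre. A reader might infer that the plan claims such proof; the text supports only that it labels this contrast as the test of H1b, and the risk follows from the label.

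*Contrast 2 is reported beside it.* With Theatre inert and d = 0.70, contrast 2 is significant in 74% (26.25 per arm) to 87% (35 per arm) of trials, and contrast 1 is significant without it in only about 11% and 7%. Readers would usually see that the arms differ. But this does not settle Theatre against the waiting list. The authors predict that H1a, H1b and H2 all hold, so contrasts 1 and 2 should both be significant, and effective PA with inert Theatre produces the same pattern.

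*Pooling need not cost power.* It may be tempting to say that contrast 1 always weakens the PA test. It does so only when Theatre is sufficiently weaker than PA; with equal effects it gains slightly. H2 predicts that Theatre is weaker, but not that it is inert.

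*The design can answer the questions.* It can: both comparisons come from the same group × time model. A reader might infer that the trial cannot test H1a or H1b, but the fault lies only in the planned contrasts.

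It is also tempting to say that H6b, which sets PA-NSS apart "compared to participants in the PA-traditional style and Theatre conditions", has the same fault. It does not. The weekly-trajectories section ties H6b to the activity-type and style effects, which are contrasts 2 and 3. If PA-NSS beats PA-TS, it lies above the PA mean; if the PA mean beats Theatre, PA-NSS beats Theatre too. Both contrasts together imply H6b. What remains is that the section joins the two effects with *or* and does not require both.

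**Conclusion.** The point holds as a mismatch between hypotheses and contrasts. H1a and H1b are both assigned to a pooled comparison, and H4 has no PA-against-waiting-list contrast either. With Theatre inert, the contrast labelled as testing H1b is favourably significant in 11% to 14.5% of trials at d = 0.35 and in 42% to 55% at d = 0.70, against 1.25% for a test of Theatre itself. In the same scenario, power for PA is 21% to 29% and 74% to 87% when tested directly, so the pooled contrast loses between a third and a half of it. That loss depends on the scenario; the missing arm-specific tests do not.

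The figures assume two-sided testing (the article does not state sidedness), equal arms, pre-post change scores with correlation 0.5, no covariate adjustment, and either no dropout or 25% dropout. The 0.70 is derived from the sample-size input and is not printed in the article.

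**What to change.** In the section on analyses of primary and secondary outcomes:

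- Prespecify two contrasts from the same fitted model, in the order WLC, Theatre, PA-TS, PA-NSS: (−1, 0, +0.5, +0.5) for H1a and H4, and (−1, +1, 0, 0) for H1b.
- Keep contrasts 2 and 3 for H2 and H3.
- If contrast 1 stays, label it *any activity against waiting list* and draw no conclusion on H1a or H1b from it.
- State how the added test shares the 0.025 per primary outcome, for example by Holm's procedure or a fixed testing order.

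Carry the arm-specific contrasts into the mediation section, because H5 concerns the effects of PA, and into the weekly-trajectories section for H6a. For H6b, say there that contrasts 2 and 3 must both be met, or estimate PA-NSS against Theatre directly.

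The cost is small. The contrasts are no longer mutually orthogonal, and each outcome has one more test, so some alpha must be shared. The edits reach three analysis sections. Design, data collection and sample size do not change.

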### Sample size

Sample size calculations were based on an a priori power analysis based on a previous study carried out on similar primary outcomes in the workplace [37, 66]. This study has reported a positive effect of the PA intervention on the emotional exhaustion component of burnout, with a small effect size (η^2^ = 0.03; f = 0.176). According to this result, we conducted an analysis with G*Power software [70] examining the evolution of burnout and vigor depending on the conditions as inter-individual factors, with an moderate effect size of d = 0.35, a statistical power of 80%, a threshold of significance at *p* < 0.025 considering our two primary outcomes, a correlation of .5 across repeated measures, and a potential dropout rate of 25% for a 10-week program with 4 groups. The results of this analysis recommend recruiting a minimum of 140 participants, 35 per group.

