### Randomization and blinding

Participants will be randomly assigned to one of the four conditions. A laboratory engineer will carry out the randomization once all participants are included, using the random function of Excel® software. Then, a second randomization will be done with the next 60 participants. A laboratory engineer will carry out the randomization, using the random function of Excel® software. In order to reduce bias, participants in PA conditions will not know their motivational style allocation (i.e. PA-TS or PA-NSS), and the instructor of each PA condition will not know the existence of the other condition. Finally, research assistants collecting data will be blinded to the treatment allocation.

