### Conditions

#### PA traditional style condition

The PA-TS condition will be composed of twenty sessions of Nordic walking over ten weeks. Participants will walk twice a week in a group of twelve people. Each session will last 60 min, including welcome, warm-up, practice, cool-down and stretching. The instructor of the PA condition (a bachelor’s degree student in sports sciences) will have been trained to teach Nordic walking to beginners as this physical activity is taught in textbooks [71]. We called this condition ‘traditional’ because the instructor will only be trained to teach the correct walking technique and will not receive any training to support the basic psychological needs of participants. He/she will receive a program plan describing the warm-up, cool-down and stretching exercises, places and the duration of the Nordic walking itself for each session.

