#### PA need-supportive style condition

In the PA-NSS condition, the organization and content of the session will be identical to the PA-TS condition. The main difference will be the motivational style implemented by the instructor. Two bachelor’s degree students in sport sciences will be both trained to deliver Nordic walking sessions using a need-supportive communication style. Grounded in SDT, the training will consist of four one-hour sessions based on SDT training [42, 72, 73] used in previous studies. In these workshops, instructors will be introduced to the main SDT postulates, will analyze video examples to identify strategies that are supportive to, and those which might frustrate, participants’ needs, and will create strategies to support participants’ needs in Nordic walking with the help of a research team member. For example, instructors will be trained to implement need-supportive strategies, such as: providing choice (e.g. type of exercise, intensity, place, route), encouraging participant input, feedback and questions; giving meaningful explanations; being empathetic and acknowledging difficulties, negative feelings or objections; being accessible, attentive and caring; trying to motivate by promoting enjoyment and the personal value of exercise or giving precise and positive feedback.

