#### Theatre condition

The Theatre condition will be composed of twenty sessions of theatre classes over ten weeks (twice a week), in a group of 15 people guided by a master’s degree student in performing arts. Each session will last 60 min, and begin with warm-up voice exercises followed by oral, theatre or improvisation exercises. The theatre sessions will include public speaking games, exercises to use the body according to context and emotions, breathing and pronunciation exercises, confidence exercises in pairs, and an introduction to improvisation exercises.

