### Strengths and Limitations

This protocol presents three main strengths. The methodological robustness constitutes the main strength of this protocol. Indeed, the comparison of four groups (three experimental groups and a waiting list control group), the subject randomization, weekly measures, and objective measures of exercise intensity respond to recommendations made by some authors [33, 98], and add a significant contribution to the literature on the effectiveness of PA interventions to improve employee well-being. Moreover, to our knowledge, this study is the first to compare the effect of PA to the effect of another leisure activity (i.e., Theatre) on burnout and vigor. Previous interventions have either focused only on the effect of PA [37] or on the effect of mixed activity programs [23, 25–27] on indicators of well-being. Another strength of this protocol is that it focuses on mechanisms that mediate the effect of activity on burnout and vigor. More precisely, we will be able to examine if specific theory-based psychological constructs (i.e., detachment, relaxation, mastery, control, relatedness, and positive affects experiences) and a physiological component (i.e., cardiorespiratory fitness) are mediators of the relationship between conditions (i.e., PA-TS, PA-NSS, Theatre condition) and outcomes. In the past, only two interventions [28, 29] have addressed some of these mediators. Our study will then be the first to test the combined influence of these different mediators. Finally, another strength of this protocol is that it tests the additive effect of an instructor’s need-supportive style based on SDT on burnout and vigor. A previous study [28] has implemented an autonomy-supportive leadership style in a PA intervention in the workplace, and indicated positive effects on work-related affective states. However, the authors compared the changes in well-being of the intervention group to a control group, but not to a traditional style PA group. Consequently, their design prevents conclusions to be developed about the respective effect of the motivational style and PA. In the present study, we will compare a traditional style PA intervention to a need-supportive PA intervention in order to disentangle the specific effect of the motivation style and PA.

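### Activities are delivered in session groups but the models have no session-group term, so standard errors for the theatre-versus-walking and style contrasts are too small if change correlates within groups

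*Protocol article*

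**What the plan says.** Under Conditions, the three activity arms are taught in groups twice a week for ten weeks. For the traditional-style walking arm (PA-TS), "Participants will walk twice a week in a group of twelve people". The need-supportive arm (PA-NSS) has the same organisation. Theatre is run "in a group of 15 people guided by a master’s degree student in performing arts". The waiting-list arm has no activity.

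The section on primary and secondary outcomes prefers mixed models partly because they respect hierarchy in the data. Its short-term model lists arm, time and their interaction as fixed effects and names no random effect. For the models with more than two time points, "we will allow random intercepts for participants and random linear slopes for the repeated measurements at the level of participants". The weekly-trajectory models likewise put a random intercept and slope at subject level. No session-group, instructor or wave term appears in the analysis sections.

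On related points, Randomization and blinding adds: "Then, a second randomization will be done with the next 60 participants". For PA-NSS, "Two bachelor’s degree students in sport sciences will be both trained to deliver Nordic walking sessions". Strengths and Limitations says that the two walking arms are compared "in order to disentangle the specific effect of the motivation style and PA".

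**The concern.** Individual randomisation makes participants independent at baseline, but not after ten weeks of shared sessions. The trial's own hypotheses give reason to expect people in one group to change alike: H3 says that the instructor's style alters outcomes, and H5e names relatedness as a mediator. Waiting-list participants share nothing comparable, so the design is partially nested.

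A model with participant-level terms only treats group members as independent. With positive within-group correlation, it understates the standard errors of contrasts involving the activity arms. Contrasts 2 (theatre versus both walking arms) and 3 (PA-TS versus PA-NSS) are hit hardest because every arm they compare is clustered. They carry H2 and H3, which the article presents as its new contributions. The stake is a false-positive rate above the 0.025 per primary outcome used in planning.

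**Working it through.** **The plan's own figure.** Sample size uses "a statistical power of 80"% and a threshold of "< 0.025 considering our two primary outcomes", with d = 0.35, correlation 0.5, four groups and 25% dropout. Take a repeated-measures within-between interaction test with f = 0.35/2 = 0.175 and m = 2 time points. The noncentrality is f² × N × m/(1 − ρ), and 80% power needs N = 111, or 112 when balanced. Then 112 × 1.25 = 140, the stated total. It reproduces, and it contains no allowance for clustering.

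**Inputs for the error rate.**
- Arm size 35 and 25% dropout (Sample size): 35 × 0.75 = 26.25, so 26 completers.
- Group sizes 12 and 15 (Conditions): 35/12 = 2.9 and 35/15 = 2.3, so three groups in each activity arm and 26/3 = 8.67 completers per group. The number of groups is derived, not stated.
- Contrast codes (Statistical analysis).
- ICC of change: not in the document; assumed 0.01 to 0.10.

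**Formulas.** The design effect of an activity arm is DE = 1 + (m − 1) × ICC, with m now the group size. For the waiting list DE = 1. The variance inflation of a contrast is VIF = Σc²DE/Σc². The actual two-sided error at nominal 0.025 is 2 × [1 − Φ(2.2414/√VIF)].

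For contrasts 2 and 3 every arm is clustered, so with equal group sizes VIF = DE. For contrast 1, Σc² = 0.5625 + 3 × 0.0625 = 0.75 and the clustered share is 0.1875/0.75 = 0.25, so VIF = 1 + 0.25 × (DE − 1).

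Example at ICC 0.05: DE = 1 + 7.67 × 0.05 = 1.383 and √1.383 = 1.176. Then 2.2414/1.176 = 1.906, giving an error of 0.057.

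| Assumed ICC | DE | Contrasts 2 and 3: true SE / model SE | Error | Contrast 1: true SE / model SE | Error |
|---|---|---|---|---|---|
| 0.01 | 1.077 | 1.04 | 0.031 | 1.01 | 0.026 |
| 0.02 | 1.153 | 1.07 | 0.037 | 1.02 | 0.028 |
| 0.05 | 1.383 | 1.18 | 0.057 | 1.05 | 0.032 |
| 0.10 | 1.767 | 1.33 | 0.092 | 1.09 | 0.040 |

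**Upper case: full groups of 12 and 15, no dropout.**

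| Assumed ICC | Contrast 1 error | Contrast 2 error | Contrast 3 error |
|---|---|---|---|
| 0.01 | 0.027 | 0.035 | 0.033 |
| 0.02 | 0.030 | 0.046 | 0.042 |
| 0.05 | 0.037 | 0.081 | 0.072 |
| 0.10 | 0.049 | 0.139 | 0.122 |

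A simulation of change scores (20,000 trials per setting; 36 per arm; walking groups of 12; theatre groups of 15, 15 and 6) agrees. At ICC 0.05 the errors for contrasts 1, 2 and 3 are 0.037, 0.075 and 0.074.

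**Wave.** In the same simulation with no clustering and arms balanced within wave, leaving wave out gives a ratio of true to model standard error of about 0.97 for a wave shift of 0.5 SD, and 0.88 to 0.90 for 1 SD. The model's standard errors are then too large, not too small.

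**The case against.** **No ICC is given, and it may be small.** The outcomes are burnout and vigor at work, not session experience. This stands: the inflation is conditional. At ICC 0.01 to 0.02 the error for contrasts 2 and 3 is 0.031 to 0.037, and contrast 1 is only modestly affected throughout. A reader might infer that the standard errors are wrong whatever the data show; the document does not support that.

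**Groups may not be fixed.** The text gives group sizes but does not say that membership is constant over the 20 sessions. If people mix, correlation is spread across groups and a simple nested term would not fit. This stands, and is why membership must be recorded.

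**The details may be in a separate analysis plan.** This does not stand. The article states the random structure for both the long-term and the weekly models, and it stops at the participant. The sentence quoted on random effects does apply only to models with more than two time points; the short-term model simply names none.

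**Two randomisation waves.** A reader might count wave as another cause of small standard errors. The calculation shows the opposite when arms are balanced within wave, and nothing in the document plans unequal allocation.

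**Instructors.** A reader might treat the instructor as a further omitted model term. With so few instructors, each tied to one arm, no term can separate person from style; this limits interpretation and is not a modelling error. A single PA-TS instructor is itself inferred from a singular noun. The blinding section also uses the singular for each walking arm although PA-NSS has two, and the limitations use the plural. The manipulation check, with blinded observer ratings and participant ratings of style, shows whether delivery differed, but it does not remove the confounding.

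**The remedy is weak with so few groups.** Three groups per walking arm leave about 4 degrees of freedom for contrast 3, with a critical t of 3.50 against 2.31 when groups are ignored. At ICC 0.05 the group variance would be estimated as zero in roughly a third of trials. This is a real cost. It reflects how little the design can say about H3, and does not justify assuming independence.

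**Conclusion.** The concern holds in conditional form. Delivery is in session groups, the specified models stop at the participant, and the trial's own mechanisms make within-group correlation plausible. If change correlates within groups, contrasts 2 and 3 are tested at more than the nominal 0.025: about 0.031 to 0.092 over assumed ICCs of 0.01 to 0.10, with 26 completers per arm and three groups per activity arm. Full groups of 12 and 15 would raise the upper end to 0.139 for contrast 2 and 0.122 for contrast 3. Contrast 1 runs from 0.026 to 0.040, or up to 0.049 with full groups.

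These sizes rest on the assumed ICC, the derived number of groups and stable membership. Wave is a matter of precision and chance imbalance. The instructor point narrows what a positive H3 result can mean.

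**What to change.** 1. Record each participant's session group. Add a partially nested random session-group effect on change (session group × time) for the activity arms only, with each waiting-list participant a singleton and Kenward-Roger or Satterthwaite degrees of freedom. State what will be reported if the variance is estimated as zero. The data cost is one identifier per participant. The statistical cost is wider intervals for contrasts 2 and 3 and a variance estimated from about three groups per arm.
2. Separately, add randomisation wave and wave × time as fixed effects, for precision and to adjust for chance imbalance. This costs two parameters.
3. In Strengths and Limitations, state that motivational style is confounded with the very few people who deliver it (apparently one instructor in PA-TS, two in PA-NSS). Word the H3 conclusion as a comparison of these instructors' delivery, supported by the observer and participant ratings of style, in place of the claim to separate style from physical activity. This needs only a change of wording.
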